## Abstract

**Background:**

At present, adherence to antipsychotic treatment is often poor, leading to the recurrence of symptoms. This increases the likelihood of the patient experiencing disability and thus increases the disease burden for the patient, their family, and society as a whole. However, to date, there is no clear evidence regarding the effect of medication adherence interventions on outcomes for patients with schizophrenia. Moreover, the traditional intervention methods are limited by manpower and resources in low- and middle-income countries. Recent studies have demonstrated that increasing a patient’s level of self-compassion may improve their treatment adherence. Online mental health care interventions have advantages in terms of feasibility and acceptability for patients with schizophrenia. In this regard, a WeChat-based self-compassion training protocol to improve patient treatment adherence was designed in this study and will be evaluated in the future to determine its impact on patients with schizophrenia.

**Methods:**

The protocol for the randomized controlled trial (RCT) is based on the SPIRIT 2013 statement. This parallel RCT will aim to recruit 392 patients with schizophrenia who will be randomized at a 1:1 ratio into a 3-week intervention or control group. Both groups will receive routine care. The intervention group will also receive WeChat-based self-compassion training, which requires participants to complete three tasks every day, including a reading task, a meditation task, and a self-compassion journal task. The control group will receive WeChat-based psychological health education, which will only require participants to read positive articles about psychological health every day. Medication adherence, self-compassion, stigma, and social support will be measured at baseline (T_0_), immediately after the intervention (T_1_), and 3 weeks after the intervention (T_2_). Program feasibility will be evaluated throughout the course of the study, and acceptability will be measured immediately after the intervention (T_1_).

**Expected results::**

The intervention described here will address the barriers to accessing mental health care for people with schizophrenia, including patients’ desire for independent management, difficulty accessing providers, and concerns about privacy and stigma. The current study provides guidance for clinical nurses to carry out psychological intervention, with the ultimate aim of addressing the problems associated with a shortage of psychological professionals in low- and middle-income countries.

## Introduction

Most guidelines recommend continuous treatment with antipsychotic medication to prevent relapse or recurrence of psychotic symptoms during the first few years following the first psychotic episode (Galletly et al., 2016; Crockford and Addington, 2017; Shimomura et al., 2020). However, studies have shown that adherence to antipsychotic treatment is often poor; between 41 and 61% of patients do not take the medication as prescribed (Valenstein et al., 2006), and the reported relapse rate is 42% due to poor medication compliance in patients with chronic schizophrenia (Acosta et al., 2009). In China, 55∼76% of patients with schizophrenia relapse because of drug withdrawal (He and Li, 2018). High recurrence not only increases the possibility of disability but also results in a serious disease burden for the families of patients and society. According to previous reports, the disability rate in schizophrenia is as high as 92.50% (Insel, 2010). Inclusion of disability when measuring disease burden has been particularly influential in highlighting schizophrenia as a leading contributor to disease burden. Observing differences in disability-adjusted life years (DALYs) demonstrates that the large burden of schizophrenia experienced in lower- and middle-income countries is around four times the burden experienced by high-income countries (Charlson et al., 2018). This is largely attributable to the significant population growth and aging of low- and middle-income countries, resulting in a greater proportion of the population of an age where the risk of schizophrenia is greatest (Charlson et al., 2018). Therefore, services to improve treatment adherence and prevent disease recurrence are important to respond to the high disability rate and disease burden among patients with schizophrenia, particularly in low- and middle-income countries.

Uzer-Kremers et al. (2020) first explored the relationship between self-compassion and treatment adherence among patients with schizophrenia in an investigation study. The results indicated that improving the self-compassion of patients with schizophrenia may increase their level of treatment adherence. Mindfulness-based interventions (Rimes and Wingrove, 2011), compassion-focused therapy (CFT) (Gilbert, 2014), and mindful self-compassion (MSC) (Neff and Germer, 2013) are training programs and intervention techniques proposed to increase a patient’s level of self-compassion. However, most of these therapies are based on group interventions, which are complex and require the input of professionals. Low- and middle-income countries lack the mental health professionals required for such interventions (McKenzie et al., 2004). Moreover, given the widespread public discrimination and prejudice against mental illness, seeking face-to-face psychotherapy is often challenging for patients with schizophrenia. With the development of the Internet, several researchers have conducted online interventions, which have advantages in terms of feasibility and acceptability and may lower the treatment-seeking threshold for patients (Josephine et al., 2017). The published literature to date also provides strong evidence for the feasibility of using smartphones to enhance the treatment adherence of people with schizophrenia (Firth and Torous, 2015). In recent years, online interventions based on self-compassion for patients with mental illness have been developed and have demonstrated positive effects. However, to date, there are no published studies to support the effectiveness of online self-compassion training among patients with schizophrenia.

## Background

While some studies of existing psychological interventions have demonstrated their effectiveness in improving medication adherence among patients with schizophrenia, including compliance therapy (CT), adherence therapy (AT), cognitive behavior therapy (CBT), and motivational interviewing (MI), other studies have reported that these interventions do not improve medication adherence (O’Donnell et al., 2003; Bechdolf et al., 2005; Barkhof et al., 2013; Schulz et al., 2013). The CT or AT or MI is multicomponent and complex, differs widely in their content and implementation, and lacks standardized interventions for patients with schizophrenia, leading to different research results (Hartung et al., 2017). Furthermore, people who are highly self-critical and shame-centered tend to respond poorly to standard CBT and consider CBT to be “emotionally heavy and unpleasant” (Barnes et al., 2013). A systematic review found no clear evidence to support the effectiveness of these medication adherence interventions on the outcomes of patients with schizophrenia (Hartung et al., 2017). Nonetheless, interventions to improve medication adherence among individuals with psychotic symptoms warrant further investigation (Hartung et al., 2017). Moreover, many of the interventions currently available require significant manpower and resources, making them less practical for low- and middle-income countries that lack these mental health professionals (McKenzie et al., 2004).

Recent theoretical developments suggest that self-to-self relating may be a critical process in the recovery of psychosis (Andrew et al., 2010). Self-to-self relating refers to the way in which individuals relate to themselves; it can be considered as an intrapersonal relationship (Andrew et al., 2010). Self-criticism causes distressing experiences of psychosis, whereas compassionate self-acceptance results in empowered action and promotes recovery and growth during psychiatric rehabilitation (Waite et al., 2015). However, during rehabilitation, patients with psychosis often adopt self-criticism to deal with their difficulties and maintain their self-esteem and self-identification (Lawrence and Lee, 2014). Highly self-critical people habitually experience feelings of inferiority, worthlessness, shame, failure, and guilt, and are often reluctant to seek support (Krieger et al., 2019). The higher the level of self-criticism, the more shame people will experience (Krieger et al., 2016). Furthermore, one-third to half of all patients with schizophrenia feel ashamed for suffering from this disease, and the stigma persists in the remission period of the disease (Gerlinger et al., 2013). Patients will select strategies such as confidentiality or isolation rather than help-seeking to avoid these feelings (Cadario et al., 2012). Stigma affects all stages of treatment, from attitude and approach to treatment plan selection (Stentzel et al., 2018). In clinical work, due to the fear of drug side effects and medicine-taking behavior that may expose their disease, patients with schizophrenia will reduce or even stop the drug themselves to avoid stigma (He, 2018).

The most common intervention that focuses on self-criticism and the stigma of mental illness is cognitive behavioral therapy (CBT), which is to challenge the content of negative thoughts, address cognitive biases in the processing of emotional information, and alleviate psychological symptoms (Vazquez et al., 2018). However, studies have shown that the influence of CBT may be overestimated (Cuijpers et al., 2016). Further, people who are highly self-critical and shame-centered tend to respond poorly to standard CBT and consider CBT to be “emotionally heavy and unpleasant” (Barnes et al., 2013). Self-compassion is a positive emotion regulation strategy and emotional arousal state (Neff and Germer, 2013). People with high levels of self-compassion tend to respond with understanding and acceptance when facing difficult emotions, rather than with avoidance (Neff and Germer, 2013). Some qualitative studies have also demonstrated the effect of self-compassion on patients with mental illnesses (Ashworth et al., 2015; Ashfield et al., 2020; Bratt et al., 2020). After completing self-compassion training, patients tend to accept rather than criticize themselves as having a problem. In recent years, scholars have demonstrated the value of self-compassion for treatment adherence in a variety of clinical populations, including patients with fibromyalgia, chronic fatigue syndrome, and cancer (Sirois and Hirsch, 2019). The relationship between self-compassion and treatment adherence among patients with schizophrenia has also been explored in an investigation study, with the results suggesting that improving self-compassion may increase the treatment adherence of patients with schizophrenia (Uzer-Kremers et al., 2020). Specifically, self-compassion supports individuals in developing a compassionate attitude toward themselves, prompting them to accept and understand their own diseases, thus reducing self-criticism and stigma and assisting in the maintenance of a positive attitude toward their responsibility for their own treatment.

There are many training programs and intervention techniques proposed to increase a patient’s level of self-compassion, including mindfulness-based interventions, MSC, and CFT. CFT was developed specifically to build the capacity to experience compassion in high-shame and self-critical individuals (Gilbert, 2014); Braehler et al. (2013) randomized patients with a schizophrenia-spectrum disorder to either a CFT group or a control group. During the 4-month CFT, compassion skills, such as mindfulness, appreciation, imagery, attention, behavior, and reframing, were practiced, and expressive writing tasks were used to help members reflect on and integrate changes in their recovery from a compassionate stance. Finally, the results support the feasibility of group CFT in psychosis and suggest that changes in compassion can be achieved.

In recent years, new forms of online interventions based on self-compassion meditation and self-compassion writing therapy for patients with mental illness have been developed and have demonstrated positive effects. The intervention time is also getting shorter [6 weeks (Finlay-Jones et al., 2017; Rodgers et al., 2018; Andersson et al., 2020), 4 weeks (Mak et al., 2018, 2019; Beshai et al., 2020), 3 weeks (Albertson et al., 2015; Toole and Craighead, 2016), 2 weeks (Kelman et al., 2018; Stevenson et al., 2019; Halamová et al., 2020, 2021; Schnepper et al., 2020; Seekis et al., 2020), and 1 week (Shapira and Mongrain, 2010) or less (Galla, 2016)]. For example, Albertson et al. (2015) randomized participants to either an intervention group (meditation via podcast) or a waitlist control group. The results indicated that the participants in the intervention group experienced significantly greater reductions in body dissatisfaction and body shame and greater gains in self-compassion and body appreciation after the 3-week meditation intervention, when compared to the control group. However, to date, there are no published studies to support the effectiveness of online self-compassion training among patients with schizophrenia. Compared with group interventions in a therapy room, online interventions can address barriers to accessing mental health care, such as patients’ desire for independent management, limited funds, time constraints, transportation issues, difficulty accessing providers, and concerns about privacy and stigma (Josephine et al., 2017). Online interventions can also reduce the use of mental health resources in low- and middle-income countries, where these resources are scarce. A recent meta-analysis demonstrated that online interventions are as effective as face-to-face interventions for a variety of psychological and physical diseases (Carlbring et al., 2018). For example, the FOCUS smartphone app is a multifaceted mobile intervention that targets auditory hallucinations, mood, sleep, functioning, and medication adherence (Ben-Zeev et al., 2013). FOCUS has demonstrated similar efficacy to standard in-person psychosocial approaches in caring for people with schizophrenia. Other smartphone apps have also been effectively designed to address social functioning in patients with schizophrenia (Fulford et al., 2021). Therefore, it is meaningful to design an online self-compassion training program specifically for patients with schizophrenia.

The existing research on self-compassion has mostly been conducted in English-speaking countries. However, self-compassion theory is, in fact, inspired by Eastern Buddhism. Studying the localization of self-compassion in China is of great practical significance, and the development of an online intervention is in line with the inadequate mental health resources in China (McKenzie et al., 2004). WeChat is a free smartphone application; it is the most widely used social networking platform in China. Similar to Facebook, WeChat public accounts can send push notifications to their followers and alert them to new content. WeChat can be used to deliver health education messages in a cheaper and more visually appealing way compared to mobile phone SMS. Studies conducted in China have shown that WeChat is effective in health promotion interventions (He et al., 2017).

Considering the importance of improving treatment adherence, the effectiveness of a high level of self-compassion, the advantages of online interventions for patients with schizophrenia, and the widespread use of WeChat among people in China, this study describes a brief WeChat-based self-compassion training protocol to improve the treatment adherence of patients with schizophrenia in China.

### Theoretical framework

The intervention program described in this study is based on four principles. First, self-compassion theory was taken as the theoretical basis. Self-compassion comprises three interacting components: self-kindness vs. self-criticism, a sense of common humanity vs. isolation, and mindfulness vs. over-identification (Neff and Germer, 2013). Self-kindness refers to the tendency to be caring and understanding toward the self rather than being harshly judgmental. Rather than attacking and berating oneself for personal shortcomings, the self is offered warmth, comfort, and unconditional acceptance. The sense of common humanity that comprises self-compassion involves recognizing that all people are imperfect, fail, make mistakes, and experience serious life challenges, rather than feeling isolated by the experience of imperfection. Mindfulness in the context of self-compassion involves being aware of one’s painful experiences in a balanced way, which neither ignores nor amplifies painful thoughts and emotions. In addition, paying attention in an equilibrated way is important; this does not involve “over-identification,” that is, being carried away by a dramatic storyline that exaggerates implications for self-worth. Therefore, we believe that patients with a high level of self-compassion tend to be caring and understanding rather than harshly judgmental about their diseases. They recognize that everyone will experience serious life challenges and be aware of their painful experiences in a balanced way, thus reducing self-criticism and stigma, and maintaining a positive attitude toward their responsibility for their own treatment.

First, the online self-compassion intervention studies in the literature were reviewed to determine the intervention content and intervention dose, including intervention form, frequency, time, and duration. The intervention aims to help participants to understand the meaning of self-compassion and to use the three components of self-compassion to help them actively cope with self-criticism and stigma, thereby improving their treatment adherence. Second, structured interviews were conducted with the target population (patients and nurses in an inpatient ward) to ensure that the program met the health needs of patients with schizophrenia and was consistent with the actual clinical situation. Third, an expert meeting (a group of eight experts including two senior doctors and two nurses in the field of schizophrenia, two psychologists, and two nursing experts) was held to ensure the scientific basis and feasibility of the intervention program. Finally, a research group meeting was conducted to identify all the detailed messages that would be published on the WeChat public account.

## Study

### Aim

The ultimate goal of this research is to evaluate the effectiveness, feasibility, and acceptability of a WeChat-based self-compassion training protocol to improve the treatment adherence of patients with schizophrenia in China. The specific objectives of the study are as follows:

#### Primary aim

To evaluate the effects of the WeChat-based self-compassion training on treatment adherence, relative to the control WeChat-based psychological health education.

#### Secondary aim

To evaluate the effects of the WeChat-based self-compassion training program on self-compassion, stigma, and social support; evaluate the feasibility of online training by examining enrollment, recruitment, retention, and journal task completion rates; and determine satisfaction and acceptability of the program by assessing eight single items on the intervention satisfaction scale.

### Design

#### Trial design

The study will be an exploratory, parallel randomized controlled trial (RCT) comparing a 3-week WeChat-based self-compassion training protocol to a control condition with only WeChat-based psychological health education. The effects of the intervention on treatment adherence, self-compassion, stigma, and social support will be evaluated among patients with schizophrenia. Eligible participants will be randomly allocated to one of the two conditions (intervention or control) at a ratio of 1:1. The Consolidated Standards of Reporting Trials (CONSORT) (Schulz et al., 2010) flowchart is presented in Figure 1. The study protocol was developed and reported according to the Standard Protocol Items: Recommendations for Interventional Trials (SPIRIT) 2013 statement (Chan et al., 2013; Supplementary File 1).

**FIGURE 1 F1:**
[figure not shown]
An overview of the study design.

#### Study setting

Participants will be recruited from the psychiatric wards at two hospitals in Hangzhou, Zhejiang, China. Both hospitals are tertiary public hospitals covering almost all patients with schizophrenia who seek medical help in Hangzhou. There is little difference in the clinical education and treatment protocols between the two hospitals. The intervention will be performed online.

#### Eligibility criteria

The research coordinator will confirm the eligibility criteria for each participant by screening their electronic medical records and communicating with the patient and their family members face-to-face.

**Inclusion criteria:**

(1)Patient must have been diagnosed with schizophrenia according to the International Classification of Diseases (ICD-10) criteria for the past year.(2)Patients must be over 18 and under 65 years.(3)Patient has achieved a curative effect that meets the clinical recovery standard according to the evaluation of psychiatrists.(4)Patient must have normal cognitive, expression, and comprehension abilities and the ability to fill in the questionnaire correctly.(5)Patient must own a smartphone and be able to use WeChat.(6)Informed consent must be obtained from the patient and one of their family members.

**Exclusion criteria:**

(1)] Patients suffering from other mental disorders.(2)Patients with severe organic brain lesions and physical diseases.(3)Patients participating in other psychological interventions.(4)Patients who have previously received clinical guidance similar to that provided in this study.

**Rejection criteria:**

The rejection criteria are as follows: patients who did not meet the inclusion criteria and who met the exclusion criteria but were mistakenly recruited into the study.

**Abscission criteria:**

(1)Patients have deteriorated mental conditions during the course of the study.(2)Patients quit the study.(3)Patients could not be contacted during the intervention, and they did not complete the intervention tasks as required.(4)Patients did not complete post-intervention evaluation.

#### Sample size

The sample size of the study was calculated using the G*Power 3.1 software package (Faul et al., 2007). With a power of 0.80, an alpha set at 0.05, and an effect size of 0.3 for the primary outcome, the Medication Adherence Rating Scale (MARS) score (Çetin and Aylaz, 2018), it was determined that each group would need 176 patients with schizophrenia. Given an attrition rate of 10%, a minimum of 392 participants (196 in each group) is required.

#### Recruitment, randomization, and allocation

Potential participants in the hospital will be identified by screening the electronic medical records on each psychiatric ward to determine those who have achieved a curative effect that meets the clinical recovery standard. These potential participants will then be contacted by a research coordinator to determine their eligibility, their ability to fill in the questionnaire, their interest in participation, their experience using WeChat, and their willingness to sign the consent form (including one of their family members). The aims of the study and participants’ right to withdraw at any time will be explained to eligible participants verbally and via an information sheet. Individuals will be able to ask the research coordinator questions about the study.

After signing the written informed consent and completing the basic demographic questionnaire and baseline evaluation, all eligible participants will be randomized to either the intervention group or the control group at a 1:1 ratio. Participants will be randomized individually using a computer-generated sequence of random numbers generated with SPSS 25. Allocation concealment will be achieved through sequentially numbered, opaque, sealed envelopes. The random sequence will be generated by an independent researcher not involved in patient enrollment and the baseline assessment. The envelope will only be opened after obtaining consent, confirming the patient’s eligibility, and performing the baseline evaluation. Then, the responsible clinical psychiatric nurses, who will facilitate the intervention in this study, will be informed of the intervention allocation. Given that the participants will either receive direct access to the WeChat-based self-compassion training or the WeChat-based psychological health education, participants will be blind to their allocation.

Participants assigned to the WeChat-based self-compassion training will receive access to the intervention WeChat group. The control group will receive access to another WeChat group. The two WeChat groups will be set with management authority such that the patients will not be able to enter the group without the consent of the responsible clinical psychiatric nurses, who will be the managers of the WeChat groups. All participants in the intervention WeChat group will be asked to scan a two-dimensional code to subscribe to and register with the “Self-compassion Tour” module of the WeChat public account. All participants in the control WeChat group will also be asked to scan another two-dimensional code to follow a WeChat public account in order to read positive articles about psychological health. Because they will not be able to register with the “Self-compassion Tour” module, they will not be able to access the information in the module. This will avoid between-group contamination through the direct sharing of messages sent via WeChat.

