### Ethical considerations

This study was approved by the Human Research Ethics Committee (REDACTED). All participants and one of their family members will be required to sign an informed consent form, which includes details of the intervention goals and procedures. Interventions and questionnaires will be conducted after written informed consent is obtained from each recruited participant. Participants will be informed of the freedom to withdraw from the study at any time and will be assured of anonymity by using special code numbers to identify themselves. All of the collected data will be pseudo-anonymized and kept confidential. Only members of the research team will be able to re-identify the participants. If the intervention proves to be effective, then participants in the control group will also receive the WeChat-based self-compassion training after the study is completed. The trial is registered at the Chinese Clinical Trials.gov.

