### Validity and reliability

This study uses a rigorous research design, an RCT with a representative and predetermined sample. It uses instruments with high validity, reliability, and statistical analysis, which can effectively reduce bias and enhance the generalizability of research results beyond the target population. Moreover, trial participants, outcome assessors (no researchers will be directly involved during data collection, as questionnaires are online), and data analysts of the research will be blinded to intervention allocation to reduce the biases in the evaluation of the effects of the intervention. The study protocol is in accordance with the SPIRIT reporting guidelines (Chan et al., 2013).

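### The protocol says participants and outcome assessors are blinded, but participants know which programme they follow and rate the primary outcome themselves

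*Protocol article*

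**What the plan says.** Under Recruitment, randomization, and allocation, the reason given for blinding is "Given that the participants will either receive direct access to the WeChat-based self-compassion training or the WeChat-based psychological health education", from which the text concludes that "participants will be blind to their allocation". Validity and reliability lists as blinded "trial participants, outcome assessors (no researchers will be directly involved during data collection, as questionnaires are online", together with the data analysts. It says that these groups "will be blinded to intervention allocation to reduce the biases in the evaluation of the effects of the intervention".

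Other parts of the same article bear on this:

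- **Disclosure before randomization.** "The aims of the study and participants’ right to withdraw at any time will be explained to eligible participants verbally", and also in an information sheet. Ethical considerations describes an "informed consent form, which includes details of the intervention goals and procedures".
- **Programme content.** Intervention patients register with a module called Self-compassion Tour and have daily reading, meditation and journal tasks. Their journals go to the nurses, who give guidance on them. Table 1 gives improving treatment adherence as the theme of week 3. Controls join a separate WeChat group and read daily articles on psychological health.
- **Nurses.** Those who facilitate the intervention are told the allocation. The article does not claim that they are blinded.
- **Primary outcome.** MARS has ten yes/no items on attitudes, beliefs and behaviour, and refers to the week before measurement (Patient adherence). At T1 and T2 the questionnaires are sent to participants by WeChat (Data collection and management).

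**The concern.** The blinding statement is an explicit claim about bias control, made twice, and the design described elsewhere in the article does not deliver it. Giving a person one of two recognisably different programmes tells them which one they have. Collecting questionnaires online removes the influence of an interviewer. It does not blind the assessor, because for MARS the assessor is the participant.

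What is at stake is how a positive result would be read. If intervention patients answer adherence questions more favourably than controls because of what they know and have just been taught, the comparison shows a difference without any difference in medicine taking. The article describes no other measure of adherence that could separate the two explanations, and Limitations does not mention the problem. A reader who relied on the stated blinding would not look for it.

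**Working it through.** **1. Does the stated reason support blinding of participants?** It would if the two programmes could not be told apart, or if participants did not know what was being tested. Neither is described. The programmes differ in name, in number of tasks (three daily tasks against reading only) and in guidance from nurses. Participants are told the aims, and the consent form covers the intervention's goals and procedures. No neutral naming or concealment of the hypothesis is mentioned.

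**2. Who assesses the primary outcome?** The article does not use the term self-reported for MARS, although it does for the other three scales. But the questionnaires go to the participant's own WeChat account and no researcher is directly involved in collection, so no other rater remains.

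**3. Is there a reason to expect reporting to differ between arms?** At T1 the one-week MARS window falls at about week 3 of the programme. For the intervention arm, that is the week devoted to adherence. The control sections listed under Intervention (challenges of mental disorder, signs of bad emotions, self-management advice) have no section named for adherence.

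**4. How large a reporting shift would matter?** The inputs from Sample size are effect 0.3 SD, power 0.80, alpha 0.05 (two-sided, from Statistical methods), 176 per arm, and 10% attrition.

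The plan's own figure comes first. By the normal approximation, n = 2(1.960 + 0.842)² / 0.3² = 174.4, so 175 per arm. The t-test version gives 175.4, so 176. Allowing for attrition, 176/0.9 = 195.6, so 196 per arm and 392 in total. The stated sample size is reproduced and is not in question.

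Now suppose that there is no true effect, but that reporting differs between arms by b SD. The documents give no value for b, so a range is assumed. In SD units the standard error of the difference is √(2/176) = 0.1066. The chance of two-sided p<0.05 is Φ(b/0.1066 − 1.96) + Φ(−b/0.1066 − 1.96).

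| Assumed shift b (SD) | b / SE | Chance of p<0.05 |
|---|---|---|
| 0 | 0 | 5.0% |
| 0.05 | 0.47 | 7.6% |
| 0.10 | 0.94 | 15.5% |
| 0.15 | 1.41 | 29.1% |
| 0.20 | 1.88 | 46.7% |
| 0.30 | 2.81 | 80.4% |

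At 196 per arm (no attrition), the figures for 0.10, 0.20 and 0.30 SD are 16.8%, 50.8% and 84.4%.

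This comparison of two means is on the same basis as the sample size calculation. The planned mixed model also uses baseline, so its precision will differ with the correlation between time points. The table shows the order of magnitude and does not predict the trial's result.

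**The case against.** The strongest defence is the comparator. Controls are not left untreated. They get their own WeChat group and public account with daily content for three weeks, and they cannot open the intervention module. Forwarding is disabled in the intervention arm, and participants are told not to share messages. Some participants, mainly controls, may not realise which programme the investigators favour. The consent text is not shown, so it cannot be said how it names or describes the two arms. This part of the defence stands. It supports partial unawareness of the hypothesis, but the article claims blindness to allocation.

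It can also be said that behavioural trials of this kind can rarely be blinded, and that this one is labelled exploratory. Both are fair. Neither makes the statement correct, and the point here does not ask for blinding.

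Several stronger readings are tempting, but the documents do not support them:

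- **That no protection of any kind exists.** The active control may mask the hypothesis in part, and analyst blinding is stated and not disputed.
- **That desirable answering occurs only in the intervention arm.** Both arms hear the aims, sit in nurse-managed groups and are offered a gift for completing questionnaires. Only the difference between arms biases the comparison.
- **That intervention patients have daily contact with a nurse.** The article describes guidance on journals and a reminder when a task is missed. It states no daily frequency of contact.
- **That the later offer to controls reveals the allocation.** Ethical considerations says that, if the intervention proves effective, "participants in the control group will also receive the WeChat-based self-compassion training after the study is completed". It does not say that participants are told this beforehand.
- **That the bias can be stated in MARS items.** The article gives no SD for MARS, so the shift is left in SD units.

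**Conclusion.** The claim that participants and outcome assessors are blinded is wrong as written. Participants know which programme they receive, and they are the assessors of MARS and of the other questionnaire outcomes. At most, some of them are partly unaware of the hypothesis.

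Differential reporting, probably larger in the intervention arm because of its week 3 theme, could produce or inflate an apparent effect. The planned effect is only 0.3 SD, so a shift of one third of it (0.10 SD) would roughly triple the 5% false-positive rate, and a shift of two thirds (0.20 SD) would bring it close to one half. These figures assume no true effect, 176 per arm and a simple comparison of means. The size of the shift is an assumption, and the documents give no evidence on how large it would be. The finding about the blinding statement does not depend on these figures.

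**What to change.** - **Recruitment, randomization, and allocation, and Validity and reliability.** State that participants and the nurses running the programmes know the allocation, and that participants are at most partly unaware of the hypothesis. State that the primary and other questionnaire outcomes are self-rated by participants who are not blinded, and that blinding is limited to the data analysts. Keep the point about online collection, but describe it as removing interviewer influence.
- **Conclusion.** Word any result as an effect on self-reported adherence.
- **Limitations.** Add differential reporting and expectation bias.
- **Optional.** Add one item at T1 asking which programme the participant believes is being tested, and report the answers by arm.

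The sample size and the planned analysis stay as they are. The cost is some rewording, one extra question if the optional item is used, and a less favourable statement of the trial's rigour. These changes do not remove the reporting bias. They stop the article from claiming a protection it lacks, and they match the conclusion to what MARS can show.
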